#### Primary outcomes

The primary outcome is the effectiveness of the intervention in reducing dry mouth complaints in patients with a life-limiting condition or frailty. This is measured by the percentage responders at week 4, for which a clinically relevant response is defined as at least a 2-point reduction on the 11-point numeric rating scale (NRS). The NRS is a frequently used instrument in both clinical practice and research settings to score symptom severity, such as for pain, nausea and sleep [31]. The NRS for dry mouth ranges from 0 = no dry mouth symptoms to 10 = worst possible dry mouth symptoms [1, 7].

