### Sample size

Sample sizes have been calculated based upon our expectation that both interventions, MEP and pilocarpine, lead to a clinically relevant lower dry mouth score, a minimum 2-point decrease on the 11-point numeric rating scale for dry mouth severity, as compared to CAU respectively placebo.

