#### Pilocarpine study

The sample size in this study was based upon our previous pilot study in older people with dry mouth [21]. By using the largest observed standard deviation from the pilot data (i.e. 3.8 points), we calculated a sample size of 57 patients per group, or 114 in total. Considering the low drop-out rates from previous studies with pilocarpine and the knowledge that in our study a less invasive administration method of pilocarpine is used, we expect limited loss-to-follow-up. However, to allow for some drop-out due to the frailty of the study population, the final sample size was set at 120 patients, with 60 patients per group.

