### Data analysis

#### Analysis of effect evaluation

All analyses will be carried out using statistical software that supports multi-level mixed model analyses, including the latest version of IMB SPSS Statistics. Demographic and baseline disease characteristic data will be summarized for each treatment group by presenting descriptive statistics. For continuous variables, we will use the mean and standard deviation (SD) in case of a normal distribution, or median and first and third quartile in case of skewed distribution. In case of missing data, we will use stochastic regression imputation to produce a synthetic part of the data to allow for an intention to treat analysis that includes all patients. For all analyses on primary and secondary outcomes a *p* value < 0.05 will be considered to indicate statistical significance. However, interpretation of these significant results will primarily focus on clinical relevance.

The primary outcome (percentage responders at 4 weeks) will be computed by using multi-level logistic regression analysis in the MEP study due to its cluster design, and linear regression analysis in the pilocarpine study taking the randomization stratification variable (sex) into account. Results will be expressed as odds ratio (OR) with a 95% confidence interval (CI).

All secondary outcome measures will be described in full using either mean and standard deviation median and interquartile range for continuous measures or count and proportion for categorical measures. Between-group differences in secondary outcomes at 4, 8, and 12 weeks (i.e., mean GOHAI-NL scores [33], mean PRFS scores [35], and patients’ Global Perceived Effect [37] dichotomized into success and no success) will be tested using multivariable generalized linear regression analysis with a link-function depending on the distribution of the variable (i.e. gaussian, or linear regression for continuous variables, binomial, or logistic regression for binary outcomes).

Cost-effectiveness analysis will be performed to examine both the costs and health outcomes of the interventions versus the control group, using the EQ-5D-5L [34], iMCQ [38] and factual costs of the medicine.

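### The pilocarpine study's yes/no primary outcome is assigned a linear regression but is to be reported as an odds ratio, which that model does not give

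*Protocol article*

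**What the plan says.** The protocol article, under Primary outcomes, defines one primary outcome for both studies: "This is measured by the percentage responders at week 4, for which a clinically relevant response is defined as at least a 2-point reduction". The scale is the 11-point NRS, and each patient either is or is not a responder.

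Under Analysis of effect evaluation, the MEP study receives a model that fits this outcome: "The primary outcome (percentage responders at 4 weeks) will be computed by using multi-level logistic regression analysis in the MEP study". The text then turns to the randomised trial and to the effect measure: "linear regression analysis in the pilocarpine study taking the randomization stratification variable (sex) into account. Results will be expressed as odds ratio (OR". The second of those two sentences names no study; it also promises a 95% confidence interval.

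The following paragraph, on secondary outcomes, gives the article's own rule for matching model to outcome: "linear regression for continuous variables, binomial, or logistic regression for binary outcomes".

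The pilocarpine sample size is argued on the score scale: "By using the largest observed standard deviation from the pilot data (i.e. 3.8 points"), giving 57 per group, or 114 in total, raised to 120. The general Sample size paragraph gives the effect for both studies as "a minimum 2-point decrease on the 11-point numeric rating scale for dry mouth severity".

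**The concern.** Outcome, model and effect measure do not fit together in the primary analysis of the double-blind trial. The outcome and the odds ratio point to logistic regression. The named model points either to a mean NRS comparison or to a risk difference. An analyst following the text must depart from it somewhere: change the model, change the effect measure, or apply the model to something other than the stated outcome. A choice of that kind on a primary analysis should be settled in writing before unblinding.

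The sample size makes it harder to dismiss the word linear as a plain slip, because it too was worked out on the NRS score. It also means that the article gives no power for the responder comparison.

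**Working it through.** **1. What each model estimates.**

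| Outcome analysed | Linear regression gives | Logistic regression gives |
|---|---|---|
| Responder, 0/1 | risk difference | odds ratio |
| NRS score | mean difference | not applicable |

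The plan combines the first row, the linear column and an odds ratio. No cell of the table matches that.

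**2. Illustration on invented data.** Take 57 patients per arm, 17 responders on placebo and 31 on pilocarpine, with sex balanced.

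- Crude risk difference: 31/57 − 17/57 = 0.246. Sex-adjusted linear regression gives a coefficient of 0.246 (95% CI 0.066 to 0.426). Its exponential, 1.28, is not an odds ratio.
- Crude odds ratio: (31/26)/(17/40) = 2.81. Sex-adjusted logistic regression gives 2.81 (95% CI 1.30 to 6.07).
- The test statistics (coefficient divided by standard error, recovered from the intervals) are about 2.7 and 2.6. The two models test nearly the same thing; what differs is the quantity reported.

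**3. The plan's own sample size.** The inputs are a difference of 2 points (Sample size), SD 3.8 (Sample size, Pilocarpine study) and alpha 0.05 (Analysis of effect evaluation). Two-sidedness is assumed. Power of 0.80 is also assumed, since the article states it only for the MEP study.

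n per group = 2 × (1.960 + 0.842)² × 3.8² / 2² = 56.7, rounded up to 57, or 114 in total.

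This matches the stated figure. One-sided alpha would give 45 per group and 90% power would give 76, so neither fits. The figure is a correct two-means calculation; it is not a responder calculation.

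**4. Power of the responder comparison at 57 per group.** The article gives no responder rates for the pilocarpine study, so two sets of assumptions are shown. The formula is

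power = Φ[(d√n − 1.96 × √(2p̄(1 − p̄))) / √(p₀(1 − p₀) + p₁(1 − p₁))],

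where d = p₁ − p₀ and p̄ is the mean of the two rates.

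*(a) Rates implied by the score-scale assumption.* Suppose that the reduction in NRS is normal, that 3.8 is its SD, and that the arms differ by 2 points. If placebo patients improve by m points on average, p₀ = Φ((m − 2)/3.8) and p₁ = Φ(m/3.8).

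- m = 0: rates 0.30 v 0.50, power 0.59
- m = 1: rates 0.40 v 0.60, power 0.60

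Power stays at 0.59 to 0.60 for m from 0 to 1.5.

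*(b) The MEP study's 25-point difference, borrowed.*

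| Placebo rate | Pilocarpine rate | Odds ratio | Power |
|---|---|---|---|
| 0.10 | 0.35 | 4.85 | 0.90 |
| 0.20 | 0.45 | 3.27 | 0.82 |
| 0.30 | 0.55 | 2.85 | 0.78 |
| 0.40 | 0.65 | 2.79 | 0.77 |
| 0.50 | 0.75 | 3.00 | 0.80 |

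For comparison, the two-means calculation at 57 per group has power 0.80.

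**The case against.** Three arguments soften the point.

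*The odds-ratio sentence may be meant for the MEP study only.* Nothing in it says so. If it is read that way, the pilocarpine study still has a linear model for a binary outcome, against the article's own rule, and is left with no stated effect measure.

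*Linear may simply be a slip for logistic.* This is plausible: the outcome, the odds ratio and the parallel MEP model all suggest it. It makes the repair easy, but the sentence still needs repair.

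*The full protocol or analysis plan may have it right.* It may. But the article states an incompatible combination here; it has not merely left out detail.

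A reader might also infer four stronger things that the article does not support.

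- *That the analysis cannot be run at all.* A sex-adjusted linear model on a 0/1 outcome can be fitted. It gives a risk difference with nearly the same test as the logistic model, as the illustration shows. Only the odds ratio is out of its reach.
- *That the choice of endpoint is open.* It is fixed. Responders are primary under Primary outcomes and again in the analysis section, and mean NRS change is listed among the secondary outcomes.
- *That omitting baseline NRS from the model is an error.* The article says only that the stratification variable is taken into account; it does not give a closed list of covariates. In a randomised comparison, leaving out a baseline covariate is not a mistake, and the article gives no figure for how strongly baseline NRS predicts response.
- *That the trial has only 60% power.* That figure needs normal change scores and needs 3.8 to be the SD of change, which the article does not say. Under the borrowed 25-point difference, power is 0.77 to 0.90.

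**Conclusion.** The point holds as a contradiction between outcome, model and effect measure in the pilocarpine study's primary analysis. It follows from the definitions of the models and from the article's own rule for binary outcomes, so it rests on no numerical assumption. The linear-for-logistic mismatch has little effect on the test itself; its effect is on which quantity is reported and on whether the primary analysis is fixed in advance.

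The sample size is a related but separate matter. Its arithmetic is right for a comparison of means under the assumptions stated above, and it was not derived for the responder outcome. The power for that outcome is unstated and depends on the assumptions: 0.59 to 0.60 under one set and 0.77 to 0.90 under the other. That range calls for a stated justification; it does not show that the trial is underpowered.

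**What to change.** Change the sentence so that the pilocarpine study's primary outcome is analysed by logistic regression of week-4 response on treatment and sex, reported as an odds ratio with 95% CI. Say explicitly that the odds ratio applies to both studies. A standardised risk difference may be added for readability. Baseline NRS, already collected at week 0, could be added as a covariate at little cost; this is optional.

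Add a sentence to the pilocarpine sample-size paragraph giving the responder rates assumed and the resulting power, and saying whether 3.8 is the SD of change or of scores.

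The cost is two sentences and no new data, provided the change is made and dated before unblinding.

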#### Mouth Education Program (MEP) study

The non-pharmacological study is a cluster non-randomized trial with 228 patients divided over twelve clusters (twelve organisations) in two care settings: a hospital setting with six clusters and a nursing home setting with six clusters. Within each care setting, three clusters will be allocated to the intervention arm on a first come, first serve basis (114 patients), after which three clusters will be allocated to the control arm (114 patients). The intervention, the Mouth Education Program (MEP), will be compared to the control, care as usual (CAU) over a twelve-week period. A cluster non-randomized design was chosen to reduce between-condition contamination and to improve recruitment and logistic processes [23].

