### Study procedures

Both studies in the DROP share the same study time frame (May 2023 – December 2024), time points for data collection and study instruments. Each participant is followed for a 12-week study period with 5 research visits (on *t* = 0, *t* = 2, *t* = 4, *t* = 8 and *t* = 12 weeks) at which questionnaires will be administered (see Table 2 and Fig. 1). At the end of the 12-week study period, a selection of patients will be asked to participate in semi-structured interviews to evaluate the received care. The screening and allocation procedures are different in both studies and are described separately below.

**Table 2 Tab2:** Data collection schedule and measurement instruments

Data collection	Measurement instrument	Visit 1 *Week 0*	Visit 2 *Week 2*	Visit 3 *Week 4*	Visit 4 *Week 8*	Visit 5 *Week 12*
Baseline characteristics	Questionnaire on patient characteristics	X				
Dry mouth severity	Numeric Rating Scale (NRS) (11-point; from 0 to 10) [1, 31]	X	X	X	X	X
Dry mouth impact	Summated Xerostomia Inventory, shortened Dutch version (sXI-D, adapted) [32]	X	X	X	X	X
Oral health-related quality of life	Geriatric Oral Health Assessment Index, Dutch version (GOHAI-NL) [33]	X	X	X	X	X
Health-related quality of life	EuroQol 5 Dimensions 5 Levels (EQ-5D-5L) [34]	X		X	X	X
Functional status	Patient-reported functional status (PRFS) [35]	X	X	X	X	X
Patient-perceived effect	Global Perceived Effect, 7-point scale [36, 37]		X	X	X	X
Patient-reported medical costs	The Institute for Medial Technology Assessment (iMTA) Medical Consumption questionnaire (iMCQ, adapted) [38]	X		X	X	X
Medication changes	Changes in medication since the last visit		X	X	X	X
Adherence^a^	Short questionnaire on adherence		X	X	X	X
Side-effects^a^	Short questionnaire on side-effects		X	X	X	X

^a^This data is collected in the pilocarpine study only

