#### MEP study

Within the MEP study, participating organizations are recruited through a regional network for nursing homes (University Network Care sector Zuid-Holland, UNC-ZH) and interprofessional connections with hospitals and nursing homes. Before the start of the study, all participating organizations are allocated to either the intervention arm (3 nursing homes, 3 hospitals) or control arm (3 nursing homes, 3 hospitals) on a first come, first serve basis (non-randomized).

Upon allocation to the intervention group, the participating nurses will first receive the MEP training before the inclusion of the first patient.

Eligible patients will be identified by the nurses and nurse specialists participating in the study with the help of the regular care teams on the wards of the hospitals and nursing homes. Identified patients will be provided with both oral and written information and an informed consent form on paper. After sufficient time for consideration (a minimum of 24 h), the patient will be asked to participate. Only after written informed consent, the study can commence.

Within the intervention group, all research questionnaires will be administered by the nurses as they are part of the anamnesis within the MEP consultation. Within the control group the questionnaires will be (telephonically) administered by a researcher.

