#### Secondary outcomes

Secondary outcomes include effect durability, (mouth-related) quality of life, patient-reported functional status, global perceived effect by participants, cost-effectiveness, adherence and side-effects. The specific research instruments per outcome used are detailed in Table 2.

Effect durability is measured by the percentage responders at week 8 and 12, as well as by changes in mean NRS dry mouth scores in the intervention versus the control group at all time-points. Effectiveness as perceived by the patient is measured by a 7-point scale (the Global Perceived Effect, GPE) [37] rating how much the patients’ condition has improved or deteriorated since the start of the study in both the control and intervention group. The global perceived effect is measured using a 7-point scale, rating how much the patients’ condition has improved or deteriorated since the start of the study for both the control and intervention group.

Changes in mouth-related quality of life is examined at all time-points between groups using two different validated questionnaires: the Geriatric Oral Health Assessment Index (GOHAI-NL) [33] and the shortened Summated Xerostomia Inventory (sXI-D) [32]. The GOHAI-NL consists of 12 oral health related items and three categories: physical function, psychosocial function and pain/discomfort. The sXI-D consists of 5 items, addressing dry mouth in general and consequences of dry mouth, such as difficulty eating and swallowing. In addition, functional status and overall quality of life are measured by a validated patient-reported functional status scale (from 0 = normal with no limitations to 4 = bed ridden, rarely out of bed) [37] and the EuroQol 5 Dimensions 5 Levels (EQ-5D-5L) questionnaire [34] respectively. The latter will also be used for the cost-effectiveness analysis and assesses quality of life in five dimensions: mobility, self-care, usual activities, pain/discomfort and anxiety/depression. The EQ-5D-5L is complemented by the iMTA (Institute for Medical Technology Assessment) Medical Consumption Questionnaire (iMCQ) for the cost-effectiveness analysis [38]. The iMCQ measures medical consumption, including medical and paramedical treatments or services, in- and outpatient care and medication.

Lastly, in the pilocarpine study the adherence and side-effects from either the pilocarpine or the placebo are measured by using short-form questionnaires.

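### Mouth-related quality of life is described as change but tested as mean GOHAI-NL at follow-up, with no stated week-0 term; if week 0 is left out, a starting gap between the non-randomised MEP arms enters the estimate

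*Protocol article*

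**What the plan says.** - **Outcome** (Protocol article, Secondary outcomes): "Changes in mouth-related quality of life is examined at all time-points between groups using two different validated questionnaires". The two questionnaires are GOHAI-NL and sXI-D. Functional status (PRFS) is introduced in the same section as something measured; it is not described as a change.
- **Test** (Analysis of effect evaluation): "Between-group differences in secondary outcomes at 4, 8, and 12 weeks (i.e., mean GOHAI-NL scores", together with mean PRFS scores and dichotomised Global Perceived Effect. These "will be tested using multivariable generalized linear regression analysis with a link-function depending on the distribution of the variable". No covariate is listed.
- **Data** (Study procedures, Table 2): GOHAI-NL and PRFS are both scheduled at week 0 and at every later visit.
- **Allocation in MEP** (Mouth Education Program (MEP) study): within each care setting, "three clusters will be allocated to the intervention arm on a first come, first serve basis", and the next three go to control. This gives six organisations per arm without randomisation. The pilocarpine study is randomised.

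**The concern.** A change and a follow-up level are different quantities unless the week-0 score enters the model. The article uses the first to describe the outcome and the second to describe the test, and it does not say how week 0 comes in.

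This matters most in MEP. Sites join an arm in order of arrival, so nothing in the design balances starting GOHAI-NL. The Study procedures section adds another possible source of a gap: nurses administer the questionnaires in the intervention arm, while a researcher does so, by telephone where needed, in the control arm. A constant effect of that difference on scores would be present at week 0 and at follow-up alike. A comparison of follow-up means without week 0 would count it, and any other lasting starting difference, as an effect of the programme.

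The other measures of effect are already anchored to the start. The primary outcome is a reduction of at least 2 points on the NRS, and Global Perceived Effect asks about change since study entry. Of the outcomes listed for this test, only GOHAI-NL and PRFS are plain levels.

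**Working it through.** **Inputs from the article.** MEP: 181 evaluable patients in 12 clusters, ICC 0.10, 20% dropout, 228 recruited. The plan's inflation reproduces: 181 / 0.80 = 226.25, so 227, and 12 × 19 = 228. These figures serve the responder outcome; no sample size or power is stated for GOHAI-NL.

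**Assumptions.** The article gives no SD, expected starting gap or week-0 to follow-up correlation for GOHAI-NL. I take a gap b of 0.1 to 0.5 patient-SDs, a within-arm correlation ρ of 0.3 to 0.7 with equal SDs at both times, and the responder ICC of 0.10 for GOHAI-NL.

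**Step 1. Is level versus change itself the defect?** Let Y be the follow-up score, X the week-0 score and τ the group coefficient. If Y = α + βX + τ·group, then Y − X = α + (β − 1)X + τ·group. The coefficient τ is the same. With week 0 as a covariate, testing the level and testing the change are one analysis. The open question is therefore whether X is in the model.

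**Step 2. Expected estimate when the intervention does nothing.**

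| What happens to the starting gap b | Follow-up means only | Change from baseline | Adjusted for week 0 |
|---|---|---|---|
| Persists in full | b | 0 | b(1 − ρ) |
| Regresses to a common mean | ρb | −(1 − ρ)b | 0 |

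For b = 0.3 with a persisting gap, the follow-up comparison gives 0.30 SD and the change score gives 0. The adjusted model leaves 0.3 × 0.7 = 0.21, 0.3 × 0.5 = 0.15 or 0.3 × 0.3 = 0.09 SD at ρ = 0.3, 0.5 or 0.7. If the gap regresses instead, the follow-up comparison still carries 0.09, 0.15 or 0.21 SD at the same correlations, and the adjusted model carries none.

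**Step 3. Chance of a false positive in MEP, follow-up means only, persisting gap, two-sided 0.05.** The design effect is 1 + (181/12 − 1) × 0.10 = 2.41. With 181 / 2 = 90.5 per arm, the standard error in patient-SDs is √(2/90.5) = 0.149 if clustering is ignored, and √(2 × 2.41/90.5) = 0.23 if it is respected. The rejection probability is Φ(b/SE − 1.96) + Φ(−b/SE − 1.96).

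| b (SD) | Clustering respected | Clustering ignored |
|---|---|---|
| 0.1 | 0.07 | 0.10 |
| 0.2 | 0.14 | 0.27 |
| 0.3 | 0.26 | 0.52 |
| 0.5 | 0.58 | 0.92 |

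With all 228 patients retained through imputation (114 per arm), the values are 0.07, 0.15, 0.27 and 0.62 with clustering respected, and 0.12, 0.33, 0.62 and 0.97 without.

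**Step 4. Precision in the pilocarpine study.** The variance of a follow-up-only comparison relative to a baseline-adjusted one is 1/(1 − ρ²). This is 1/0.75 = 1.33 at ρ = 0.5, 1/0.64 = 1.56 at 0.6, and 1/0.51 = 1.96 at 0.7.

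**The case against.** The strongest reply is that the regression is called multivariable. It therefore has covariates, week-0 GOHAI-NL is an obvious one, and a condensed article may leave the list to the full protocol or analysis plan. This stands as far as it goes: nothing in the text excludes baseline, so a reader who infers that the MEP effect will be biased goes beyond the document. It does not settle the point, because the article does fix a description of the outcome and a description of the test, and the two agree only if week 0 is a covariate. The same section names the terms it relies on for the primary outcome: the multi-level structure in MEP and sex in the pilocarpine study.

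It can also be said that the description of change is narrative and defines no change-score variable. That is fair, and Step 1 shows that the wording would be harmless with week 0 in the model.

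Three stronger readings are not supported:

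- **PRFS as a second contradiction.** The article never describes PRFS as a change. Only the general case for baseline adjustment applies.
- **The 0.23 SD as bias.** It is also the SD of a chance baseline difference between arms. Chance imbalance is sampling error, and a cluster-aware standard error already contains it. The figure also borrows the ICC of another outcome. Bias would come from systematic differences between sites or in how questionnaires are administered, and the documents do not quantify these.
- **Bias in the pilocarpine study.** Randomisation protects the follow-up comparison there. Only precision is lost.

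The Limitations section concedes that the non-randomised design may introduce some bias, but says nothing on starting scores.

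**Conclusion.** The point holds in conditional form. The outcome and test descriptions for GOHAI-NL do not match as written, and the week-0 score that would reconcile them is collected but not named.

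If it is left out, the MEP comparison carries all of a persisting starting gap, or a fraction ρ of one that regresses. The false-positive probability for a persisting 0.3 SD gap is about five times the nominal level with clustering respected (0.26/0.05) and about ten times without (0.52/0.05). These sizes rest on assumed gaps and on the responder ICC; they show sensitivity and do not forecast what the trial will find.

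Naming the covariate is a real improvement but not a complete cure in MEP, since about b(1 − ρ) of a persisting gap remains. The primary outcome is not affected. The matter deserves correction because it bears on the stated aim concerning oral-health-related quality of life.

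**What to change.** In Analysis of effect evaluation:

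1. State that GOHAI-NL at weeks 4, 8 and 12 is modelled with the patient's own week-0 score as a covariate in both studies, and that the baseline-adjusted between-group difference is reported. The test then matches the description in Secondary outcomes.
2. Do the same for PRFS, as a gain in comparability and precision.
3. For MEP, report the between-group difference in change from baseline as a sensitivity analysis, and acknowledge that adjustment may leave part of a persisting gap. Step 2 shows why both are informative: change is free of a gap that persists, adjustment is free of one that regresses, and the data may lie between.

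The cost is two or three sentences and one covariate per outcome. The scores are already scheduled at week 0, and neither sample size changes.

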#### MEP study

For this study, we expect the intervention group (patients who follow the MEP) to have at least 25% more responders (patients with clinically relevant less dry mouth at 4 weeks) than in the control group (patients who receive CAU). To test the null hypothesis (expected difference in responders at 4 weeks of 25%) with a power of 0.8, an alpha of 0.05 and an intra cluster coefficient of 0.10, we will need to include 181 patients which is obtained in 12 clusters (six hospitals and six nursing home clusters). Taking into account a 20% dropout rate at 4 weeks due to the frailty of our study population, 228 patients are needed. Each participating center is therefore expected to include 19 patients.

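### In the MEP study, GOHAI-NL, PRFS and Global Perceived Effect are assigned a regression with no cluster term, although whole organisations are allocated and the primary outcome gets a multi-level model for that reason

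*Protocol article*

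**What the plan says.** The MEP study is a "cluster non-randomized trial with 228 patients divided over twelve clusters (twelve organisations) in two care settings" (Methods, Study design, MEP study). Within each care setting, "three clusters will be allocated to the intervention arm on a first come, first serve basis (114 patients"), and three more go to control. That makes six organisations against six, balanced by setting.

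The sample size for the 4-week responder outcome is set "with a power of 0.8, an alpha of 0.05 and an intra cluster coefficient of 0.10" (Methods, Sample size, MEP study). It arrives at 181 evaluable patients, raised to 228 for dropout, or 19 per centre.

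Under Data analysis, Analysis of effect evaluation, the primary outcome "will be computed by using multi-level logistic regression analysis in the MEP study due to its cluster design", and the pilocarpine study has its own single-level model. The following paragraph turns to secondary outcomes at 4, 8 and 12 weeks, listing mean GOHAI-NL, mean PRFS and dichotomized GPE. Group differences "will be tested using multivariable generalized linear regression analysis with a link-function depending on the distribution of the variable", spelled out as linear regression for continuous outcomes and logistic regression for binary ones. This paragraph does not separate the two studies. It names no random effect, generalized estimating equation or cluster-robust error. The 0.05 threshold applies to secondary as well as primary outcomes.

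**The concern.** The secondary outcomes come from the same patients in the same organisations as the primary outcome, so the reason given for a multi-level primary model applies to them too. A single-level regression treats all MEP patients as independent. When patients of one organisation resemble each other, it understates the standard error of the arm difference. P values are then too small and 95% confidence intervals too narrow. At stake are the MEP conclusions on oral-health-related quality of life, functional status and patient-perceived effect.

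This is more than detail left to an analysis plan. The article names a model, and for a trial that allocates clusters it is unsuitable as named. An analysis plan that followed it would carry the error over.

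**Working it through.** **Inputs from the article.** Twelve clusters, six per arm; "an intra cluster coefficient of 0.10"; 181 evaluable and 228 enrolled patients; 20% dropout; threshold 0.05. Sidedness is not stated, so two-sided is assumed.

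**The plan's own figure.** 181 / (1 - 0.20) = 226.25, so 227. Rounded up to equal clusters, 12 × 19 = 228, which reproduces the stated total. The 181 cannot be checked because no control response rate is given, but nothing below depends on how it was derived.

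**Cluster size m.** Evaluable: 181 / 12 = 15.1. Enrolled: 19. The larger value is relevant because the article plans imputation to keep all patients in the analysis.

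**Formulas.** Design effect DE = 1 + (m - 1) × ICC. The single-level standard error is too small by a factor √DE. The actual type I error of a nominal two-sided 5% test is 2 × [1 - Φ(1.96 / √DE)].

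**At ICC 0.10:**
- m = 15.1: DE = 1 + 14.1 × 0.10 = 2.41; √DE = 1.55; 1.96 / 1.55 = 1.26; type I error 20.7%, interval coverage about 79%.
- m = 19: DE = 1 + 18 × 0.10 = 2.80; √DE = 1.67; 1.96 / 1.67 = 1.17; type I error 24.2%, interval coverage about 76%.

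**At smaller ICCs:**

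| ICC | m = 15.1: DE, type I error | m = 19: DE, type I error |
|---|---|---|
| 0.05 | 1.70, 13.3% | 1.90, 15.5% |
| 0.02 | 1.28, 8.3% | 1.36, 9.3% |
| 0.01 | 1.14, 6.7% | 1.18, 7.1% |

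**Simulation under the null, 12 clusters, ICC 0.10.** Linear regression rejected in 20.6-21.3% of runs (m = 15) and 24.2-24.9% (m = 19), with or without a setting covariate. Logistic regression depends on the scale of the ICC. With 0.10 on the observed proportion scale, rejection was 20.1-20.7% and 24.2-25.3%. With 0.10 on the latent logit scale, it was about 16-20%, because the observed-scale ICC is then only about 0.07. A t-test on the 12 cluster means held 4.9-5.0%, so valid inference is feasible with this number of clusters.

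**If part of the ICC is a setting difference.** Each arm has three hospitals and three nursing homes, so a hospital versus nursing home difference cancels from the arm contrast. The article does not give the split, so the following shares are assumptions. Take a total ICC of 0.10 with care setting in the model:
- Half due to setting: remaining ICC = 0.05 / 0.95 = 0.053; DE = 1.74 to 1.95; type I error 13.7% to 16.0%.
- Four fifths due to setting: remaining ICC = 0.02 / 0.92 = 0.022; DE = 1.31 to 1.39; type I error 8.6% to 9.7%.

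Simulation, again with assumed shares, gave 13-16% and 7-10%. With setting in the model, DE exceeds 1 for any positive ICC within setting, so the error stays above 5%.

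**The case against.** The strongest reply is that the article never says clustering will be ignored. One condensed sentence covers two trials of different design and mainly explains how the link function is chosen. The same section opens by requiring software that can fit multi-level mixed models. That leaves some chance that a multi-level version was meant. But the requirement concerns software, and where the authors wanted a multi-level model they named it and gave the reason. Read as written, the secondary model is single-level.

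Other replies limit the size and reach of the point, and they stand:
- The ICC of 0.10 is the planning value for the 4-week responder outcome. No ICC is given for GOHAI-NL, PRFS or GPE. A reader might infer that these tests have a 20-25% false-positive rate outright; the article supports this only conditionally.
- Setting is balanced across arms, so the 0.10 figures assume that all of the ICC lies within setting.
- A reader might extend the point to every MEP secondary outcome, including effect durability. The sentence lists only GOHAI-NL, PRFS and GPE. Durability (responders at weeks 8 and 12, and mean NRS) and sXI-D are not in that list.
- A reader might conclude that the primary analysis by contrast handles the clusters correctly. It is multi-level, but no small-sample correction for 12 clusters is stated for it either, so the article does not establish this.
- By weeks 8 and 12, clusters may hold fewer than 15 patients if missing values are not imputed, which lowers the inflation somewhat.

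The article also says interpretation will rest mainly on clinical relevance. That does not repair the confidence intervals, which would be too narrow as well.

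**Conclusion.** The point holds for GOHAI-NL, PRFS and dichotomized GPE in the MEP study: the named model does not fit the cluster allocation. If an ICC of 0.10 applied to these outcomes within care setting, with 15 to 19 patients per cluster, the nominal 5% test would have about 21-24% type I error, or about 16-20% for a binary outcome if the ICC is on the latent scale. It would be about 13-16% at ICC 0.05 and 8-9% at 0.02. A hospital versus nursing home share of the ICC brings the error below the 0.10 figure. With setting in the model, it stays above 5% for any positive within-setting ICC. The primary MEP analysis and the pilocarpine study are not affected by this sentence.

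**What to change.** State that in the MEP study GOHAI-NL, PRFS and dichotomized GPE are analysed with linear or generalized linear mixed models with a random intercept for organisation, or with an equivalent cluster-level analysis, using inference suited to 12 clusters. Include care setting as a fixed effect. Adjust for the baseline value where one is collected: Table 2 has a week-0 value for GOHAI-NL and PRFS, but none for GPE. Say that the single-level model applies to the pilocarpine study only.

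This is a change of wording. It needs no new data, and the article already requires software that can fit such models. The cost is wider confidence intervals for these MEP comparisons. At ICC 0.10 within setting, the standard errors would be about 1.55 to 1.67 times those of the single-level model, before any small-sample correction.
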